## Abstract

**Background:**

Patients with unresectable advanced cutaneous squamous cell carcinoma (cSCC) are generally treated with palliative intent. Immune checkpoint blockade has significant activity in the palliative setting in patients with recurrent or metastatic cSCC. This single arm phase 2 prospective study aims to investigate the combination of curative intent chemoradiation and durvalumab (anti-PD-L1 checkpoint inhibitor) for this patient cohort.

**Methods:**

Patients with unresectable locally and or regionally advanced pathologically confirmed cSCC (stage III-IVa) deemed fit for CRIO by consensus of the Multidisciplinary meeting will be eligible. In the first stage of a two-stage minimax design, we aim to recruit a total of 15 patients. If fewer than 7 patients achieved a complete response in the first stage, we will conclude the treatment is not more effective than standard treatment. The co-primary endpoints of CRIO are the safety of treatment (acute and late toxicities) and the rate of complete response. Secondary endpoints would include overall survival, progression free survival, and locoregional control. Translational research endpoints including biomarkers (CD73, CD39, PD-1, PD-L1) will also be explored utilising multiplex immunohistochemistry on tumour biopsy samples obtained prior to commencing treatment and during treatment (week 2). In addition, the utility of CXCR-4 PET/CT scan will be explored.

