#### Sample size

A two-stage minimax design will be applied, which requires an initial sample of 15 patients, with possibly an additional 13 patients required (total 28) subject to feasibility. The hypothesis that the proportion responding is 70% or more compared to the alternative hypothesis that 50% or fewer respond will be tested using a two sided binomial test with a target significance level of 0.10 and power of 0.80. Fifteen patients would be recruited in the first stage and if 7 or fewer patients respond the trial will be terminated and we will conclude that the treatment is not more effective than standard treatment. If 8 or more patients respond, the trial may go to the second stage, recruiting a further 13 patients. Of the total of 28 patients, 18 or more must respond to the treatment to be considered better than current treatment. Sample size was calculated using the PASS 13 Power Analysis and Sample Size Software (NCSS, 2014).

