### Statistical methods

#### Statistical methods for primary and secondary outcomes

For the first stage, the analysis will focus on descriptive statistics. Categorical variables will be summarised using frequencies and percentages and continuous variables will be summarised using means with standard deviations or as medians with interquartile ranges. Median survival time (with 95% CI) will be described and survival time will be presented using a Kaplan–Meier curve. Safety/toxicity data will be presented according to the frequency of occurrence. The proportion of patients experiencing the primary outcome (complete response) will be presented with 95% confidence intervals and compared to the hypothesized null effect of 0.5 using an exact binomial test.

Secondary outcomes including overall survival, disease free survival, time to progression and loco-regional control will be presented using a Kaplan–Meier curve.

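### The abstract and the sample size section set different stage 1 futility boundaries, so a result of exactly 7 responses in 15 has no single outcome

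*Protocol article*

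**What the plan says.** The article states the stage 1 rule twice.

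- **Abstract, Methods.** The treatment is judged no better than standard "If fewer than 7 patients achieved a complete response in the first stage". With 15 patients that covers 0 to 6 responses.
- **Sample size.** Among the same 15 patients, "if 7 or fewer patients respond the trial will be terminated", and the same conclusion of no advantage over standard treatment follows. The other side is also given: "If 8 or more patients respond, the trial may go to the second stage". This covers 0 to 7 on one side and 8 to 15 on the other.

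The Sample size section also fixes the rest of the design: 15 patients, then 13 more, 28 in all, with at least 18 responses of 28 needed for success. The Interim analyses section says that none is planned, so it does not help to decide between the two boundaries.

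**The concern.** Both sentences state the futility rule for the same patients and the same endpoint, complete response, but they differ by one response. At 7 of 15, the Sample size section terminates the trial. Under the abstract, 7 lies outside the futility region, so the trial would be free to go on.

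This is the only numerical rule for entry to stage 2. The trial is single-arm and unblinded, so if 7 occurs, the choice of sentence to follow would be made with the result in view. Going on would mean treating up to 13 more patients after a result for which the detailed section calls for termination. A later reader could also cite either sentence to argue that the trial had kept or broken its rule.

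**Working it through.** **Inputs**

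- Design: "A two-stage minimax design will be applied, which requires an initial sample of 15 patients, with possibly an additional 13 patients required (total 28"), so n1 = 15, n2 = 13, N = 28 (Sample size).
- Response rates 0.50 and 0.70 (Sample size). The null is p0 = 0.50, confirmed under Statistical methods: "compared to the hypothesized null effect of 0.5 using an exact binomial test". Hence p1 = 0.70.
- Error rates: "two sided binomial test with a target significance level of 0.10 and power of 0.80" (Sample size).
- Final success: at least 18 of 28 (Sample size).
- Stage 1 boundary r1 (stop if X1 ≤ r1): 7 in Sample size, 6 in the abstract.

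**Step 1. Reproduce the stated design.** For a two-stage rule that stops if X1 ≤ r1 and otherwise declares success if the total is at least 18:

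P(success | p) = Σ over x from r1 + 1 to 15 of P(X1 = x) × P(X2 ≥ 18 − x), with X1 ~ Bin(15, p) and X2 ~ Bin(13, p).

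An exhaustive search was run for the smallest N with power of at least 0.80, taking the lowest expected N under p0 among ties.

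| One-sided alpha limit | Stop at or below | Fail at or below | Alpha | Power |
|---|---|---|---|---|
| 0.10 | 7 of 15 | 17 of 28 | 0.0900 | 0.8009 |
| 0.05 | 12 of 23 | 23 of 37 | 0.0482 | 0.8011 |

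The first row is the Sample size rule exactly: stop at 7 or fewer, succeed at 18 or more.

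**Step 2. Probability of the disputed result.** P(X1 = 7) = C(15,7) p^7 (1 − p)^8, with C(15,7) = 6435.

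- p = 0.50: 6435 / 32768 = 0.1964. By symmetry 8 has the same probability, so 7 and 8 are the joint most likely results.
- p = 0.60: 0.1181.
- p = 0.70: 0.0348.

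**Step 3. Early stopping and expected N under the null.** E[N] = 15 + 13 × (1 − P(stop)).

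- Stop at ≤ 7: P(stop | 0.50) = 16384 / 32768 = 0.5000; E[N] = 15 + 13 × 0.5000 = 21.5.
- Stop at ≤ 6: P(stop | 0.50) = (16384 − 6435) / 32768 = 0.3036; E[N] = 15 + 13 × 0.6964 = 24.05.

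**Step 4. Overall operating characteristics, success at ≥ 18 of 28 in both.**

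| Boundary | Alpha | Power | P(stop at 0.50) | P(stop at 0.70) | E[N] at 0.50 |
|---|---|---|---|---|---|
| ≤ 7 (Sample size) | 0.0900 | 0.8009 | 0.500 | 0.050 | 21.5 |
| ≤ 6 (abstract) | 0.0922 | 0.8079 | 0.304 | 0.015 | 24.05 |

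**Step 5. What continuing at 7 would gain.** From 7, success needs 18 − 7 = 11 or more responses among 13.

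- p = 0.50: (78 + 13 + 1) / 8192 = 0.011.
- p = 0.70: 0.139 + 0.054 + 0.010 = 0.202 (unrounded terms).

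These account for the shifts in Step 4: 0.1964 × 0.0112 = 0.0022 for alpha and 0.0348 × 0.2025 = 0.0070 for power.

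**The case against.** The strongest reply is that the detailed section is complete and consistent in itself: it gives the action on both sides of the boundary, with no gap or overlap. The abstract is a summary sentence that never mentions stopping or continuing, so continuation at 7 is only inferred from it. That is true, but the inference is a fair one: the abstract draws the same conclusion that the Sample size section ties to termination, and gives a specific number for it. The article does not say that one section takes precedence.

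A second point is that both boundaries satisfy alpha 0.10 and power 0.80 with 28 patients, so the stated error rates alone do not rule out the abstract's version. This stands. What selects 7 is the usual minimax convention of taking the lowest expected N under the null among designs with the same maximum (21.5 against 24.05). The match also requires 0.10 to be a one-sided level, although the section calls the test two-sided. That label is a separate matter.

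Third, the consequences are limited. Alpha differs by 0.2 percentage points and power by 0.7. Entry to stage 2 is discretionary in any case, and a data safety monitoring committee reviews safety and efficacy every six months. These facts bound the damage, but they do not tell anyone what to do at 7 of 15.

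**Conclusion.** The concern holds. The two statements of the stage 1 boundary cannot both be right at 7 of 15, a result with a 19.6% chance if the combination adds nothing to the 50% response rate, 11.8% at a true rate of 0.60 and 3.5% at 0.70. The Sample size boundary is the one that the design calculation gives, on two assumptions: that alpha 0.10 is one-sided, and that ties at N = 28 were broken by expected sample size under the null. The abstract is therefore most likely the error.

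The main cost of following the abstract would be a weaker futility stop: a truly ineffective treatment would be stopped early 30.4% of the time and not 50.0%, with 24.05 − 21.5 = 2.55 more patients on average. Type I error and power stay within target under either boundary, and the success threshold of 18 of 28 is unaffected. It still must be corrected, because a pre-specified stopping boundary has to give one answer before the stage 1 result is known.

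**What to change.** Amend the Methods paragraph of the abstract so that it carries the Sample size rule: 7 or fewer complete responses among the first 15 patients ends the trial with the futility conclusion, and 8 or more allows stage 2. Check any other summary of the trial for the same slip; none was available here. If stage 1 has already been evaluated, record which boundary was applied and when that was decided.

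The cost is a one-line correction, with no change to the sample size, the design or the analysis.

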**Discussion:**

CRIO is a novel trial evaluating the combination of curative intent chemoradiotherapy with concurrent and adjuvant durvalumab for patients with unresectable stage III-IVa cSCC.

*Trial registration*: Trial registered with the Australian New Zealand Clinical Trial Registry (ACTRN12618001573246)

## Background

Cutaneous squamous cell carcinoma (cSCC) of the skin is the second most common skin cancer (after basal cell carcinoma). Lifestyle changes in the last 50 years have led to increased exposure to sunlight provoking a sharp rise in its incidence worldwide. Australia has one of the highest incidence of cutaneous skin malignancies in the world [1]. Early cSCC is often curable with local therapy. Metastases are rare, but spread to regional lymph nodes or more distant sites occurs in 5–10% of patients and confers a poor outcome [2, 3]. Presentations with locally advanced primary disease and/or regional nodal metastases (Stage III and IVa, AJCC 8th edition) [4] is not uncommon and patients face the grim prospect of morbid surgery or uncontrolled loco-regional disease affecting critical areas in the head and neck. Current standard of treatment is surgery followed by adjuvant radiotherapy. However, a proportion of patients cannot undergo surgery due to significant medical comorbidities which put them at high risk of intraoperative mortalities. This group of patients are categorised to have medically unresectable disease. Some patients have diseases that the MDT consensus is that R0 resection is unlikely to be achieved. For example, big nerve perineural diseases closely related to critical organs such as spinal cord or brain stem; extensive dermal spread of cSCC; nodal diseases encasing the carotid arteries. Some patients refuse to undergo surgery due to the consequential functional and/or cosmetic morbidities following total rhinectomy and/or orbital exenteration or other forms of extensive cranio-facial resections. For the purpose of this study, patients refused to have mutilating surgery and/or residual diseases anticipated due to proximity to critical organs at risk are categorised to have surgically unresectable disease.

Patients with stage III-IVa unresectable diseases can be treated with single modality radiotherapy or immunotherapy. It is anticipated that locoregional control and cure rates would be very low with single modality radiotherapy [5].

The use of concurrent chemotherapy with radiotherapy for cSCC in the definitive setting has been investigated in several retrospective series, with most utilising cisplatin-based chemotherapy. Results indicated partial response between 17 and 54% and complete responses in 17 to 43% [6–9]. Our institution has published the only prospective study of definitive chemoradiation in this setting. This demonstrates a 50% rate of complete response with combined radiotherapy and concurrent cisplatin/carboplatin [10]. Complete responders after definitive chemoradiation rarely recur in the irradiated area. It is therefore logical to consider adding an agent to improve on the 50% complete response rate.

cSCC has several clinical and biological factors which suggests it is appropriate for the clinical study of inhibition of the Programmed Death-1/Programmed Death-Ligand 1 (PD-1/PD-L1) immune check point: high mutation burden [11] presence of tumour-infiltrating-lymphocytes [11–14], association with immunosuppression as a risk factor [15], evidence of direct immunosuppressive effects of UV radiation [16], and some clinical efficacy with interferon 2α-based treatment [17]. The presence of high mutation burden is also a common characteristics of other solid tumours for which inhibition of the PD-1/PD-L1 axis has been associated with therapeutic efficacy, including melanoma, non-small cell lung cancer, and urothelial cancer [18].

The use of PD-1/PD-L1 immune check point inhibitor is generally well tolerated and publications of prospective phase 2 studies [19, 20] on cemiplimab have shown impressive response of patients with recurrent advanced/metastatic cSCC being sensitive to PD-1 blockade. The survival benefit of adding immunotherapy to chemoradiation is also evident in the setting of locally advanced non-small cell lung cancer as shown in a randomized controlled trial [21]. Durvalumab (MEDI4736) is a human monoclonal antibody of the immunoglobulin G-1 kappa subclass that inhibits binding of PD-L1. As Durvalumab (MEDI4736) is an engineered monoclonal antibody, it does not induce antibody-dependent cellular cytotoxicity or complement-dependent cytotoxicity.

We hypothesize the addition of durvalumab will improve the rate of complete response to definitive chemoradiation for patients with unresectable stage III-IVa cSCC. The CRIO study aims to primarily investigate and report the efficacy (rate of complete response) and safety (incidence of treatment related toxicities) of this novel therapeutic approach. The rate of progression free survival, locoregional control, and overall survival will also be reported as the secondary outcome.

Translational research endpoints including biomarkers will also be explored utilising multiplex immunohistochemistry on tumour biopsy samples obtained prior to commencing treatment and during treatment (week 2). In addition, the utility of CXCR-4 PET/CT scan will be explored. Participation in the translational study is optional. Similarly, participation in the CXCR-4 PET/CT study will also be optional. Patients will receive the same treatment regardless of their participation in the translational and CXCR-4 PET/CT sub-studies.

### Objectives

The primary objectives were toAssess the safety of treatment (treatment related acute and toxicities) and toAssess the rate of complete response.

The secondary objectives were to assess overall survival, progression free survival, and locoregional control. In addition, the correlation of CXCR-4 uptake on PET/CT scan (see below in Study setting) to overall survival, progression free survival, and locoregional control.

## Methods/design

CRIO is a single arm, non-blinded, prospective, phase II study with a two-stage minimax design in a single Australian academic hospital.

### Methods: participants, interventions and outcomes

#### Study setting

This trial is a single arm, phase II, prospective study conducted in a single Australian academic hospital in Queensland. Data will be collected at the hospital where patients are being accrued.

#### Translational studies

Adenosine is generated in response to proinflammatory stimuli such as cellular stress initiated by hypoxia or ischemia [22, 23]. Release of extracellular ATP undergoes conversion to AMP by the enzyme CD39 and subsequent dephosphorylation of AMP to adenosine is catalyzed by CD73. Adenosine signaling, particularly via the A2A adenosine receptor, potently reduces effector functions of cytotoxic lymphocytes (CD8+ T cells and NK cells) while also promoting recruitment and polarization of immunosuppressive cell types, including myeloid-derived suppressor cells and T regulatory cells [24]. Previously, we and others have identified that targeting adenosine generation by blockade of the ectonucleotidase CD73 or downstream A2AR inhibition enhances tumour control and anti-metastatic activity [25–28]. In addition, therapeutic approaches targeting the adenosinergic pathway alongside immune checkpoint blockade and chemotherapies display enhanced anti-tumour efficacy in combination [22, 29–31]. Importantly, targeting adenosine in solid tumours using anti-CD73 (NCT02503774) or A2A adenosine receptor antagonism (NCT02403193 and NCT02655822) has entered clinical trials.

We previously demonstrated that in more advanced clinical stage, CD73 expression is increased in cutaneous melanoma patients who did not receive any immunotherapy or BRAF/MEKi. In this present study, we aim to evaluate if the adenosinergic pathway is present in cSCC and its relationship with the PD-1/PD-L1 pathway. We will utilize multiplexed immunohistochemistry to evaluate the expression of CD73, CD39, PD-1, PD-L1 on tumour, endothelial or immune cells on tumour biopsies to examine cellular aspects of response. These biopsies will be obtained at baseline and if feasible, biopsies will also be obtained at week 2 while patients are on treatment. Furthermore, all patients will have serial blood sampled (baseline, weeks 3, 13, 21 and 37) for retrospective immunological and molecular studies should funding be obtained. This will include FACS analysis for innate and adaptive immune cell, and their expression of activatory and inhibitory receptors. mRNA can be isolated and immune signatures assessed using either a Nanostring panel or RNAseq. The clonality of T-cells can be examined by sequencing the TCR using Illumina-based next generation sequencing.

Results could provide the first proof-of-principle clinical evidence of the prognostic relevance of the density of immune cell infiltration, and presence of the adenosinergic pathway in cSCC.

Participation in the translational substudies is optional. Patients will receive the same cancer treatment regardless of their participation.

### CXCR4 PET/CT scan as a pilot sub-study

CXCR-4 is a chemokine receptor identified to promote the metastasis of a variety of cancer, including mucosal head and neck SCC. The over-expression of the CXCL12/CXCR4 chemokine system is likely to play a role in several tumour promoting effects including metastasis and resistance to treatment [32]. Promising human trial results for antibodies targeting other T-cell immunosuppressive mechanisms (e.g. immune checkpoints PD-1/PD-L1 and CTLA-4) have been reported for several cancers. A recent preclinical study demonstrated that targeting CXCR4 through inhibitory antibodies, in combination with anti-PD-L1, caused tumour regression in a mouse model of cancer which is resistant to PD-1 and CTLA-4 blockade [33]. This provides a good rationale for exploring the relationship between CXCR4 and immunotherapy, of which little is known in human SCC.

At the Herston Imaging and Research Facility within our institution, we have access to a novel Positron Emission Tomography (PET/CT) tracer, 68Ga-CPCR4-2 (68Ga-Pentixafor) which binds to CXCR4 receptors. It is hypothesized that cutaneous SCC with higher CXCR4 uptake would be at greater risk of nodal and distant metastases. As a pilot sub-study, we aim to explore the utility of CXCR4 in predicting the response to CRIO. Participation in the CXCR4 pilot sub-study is optional and all patients enrolled in the CRIO study will be treated and followed up the same way. The information obtained from the CXCR4 pilot study is hypothesis generating given the likely small patient number. If a trend is detected in its predictive utility, this may lead to the use of CXCR4 PET/CT for cSCC in future trials.

Participation in the CXCR-4 PET/CT substudy is optional. Patients will receive the same cancer treatment regardless of their participation.

#### Eligibility criteria

Inclusion criteria were as follows: adult patients presenting with pathologically confirmed unresectable* cSCC with locally-advanced disease at the primary site with or without metastases to the nodal regions, or advanced regional lymph node metastases of presumed skin origin, or unresectable perineural disease (stage III-IVa); Eastern Cooperative Oncology Group performance status 0–2; and assessable disease. Patients with bulky disease are assessed using RECIST criteria. Patients with perineural disease must have disease visible on imaging or biopsy-proven disease.

Exclusion Criteria include: Immunosuppression secondary to haematological malignancy or the use of immunosuppressant following solid organ transplantation; active infection requiring therapy with HIV, Hepatitis B or C virus; active uncontrolled bleeding; previous chemotherapy and/or radiotherapy to the head and neck region which would preclude re-treatment; contra-indication for radiotherapy or chemotherapy; claustrophobia; previous treatment with a PD1 or PD-L1 inhibitor; receipt of anticancer therapy 60 days prior to the first dose of study drug; use of immunosuppressive medication within 14 days before the first dose of Durvalumab (MEDI4736); any unresolved toxicity NCI CTCAE v 4.03 Grade ≥ 2 from previous anticancer therapy; history of allogenic organ transplantation; active or prior documented autoimmune or inflammatory disorders and receipt of recent live attenuated vaccine.

*The definition of unresectable disease:Medically unresectable: Patients likely to have high rate of intra/peri-operative morbidities or mortalities seconcry to significant medical comorbiditiesSurgically unresectable as per the sub-specialty MDT consensus that R0 resection is unlikely to be achieved. Examples:Patients with diseases closely abutting critical organs at risk such as brainstem and/or spinal cord as in the setting of big nerve perineural spread;Patients with rapid dermal metastases at presentation where clear margins can not be safely achieved and/or disease is expected to recur rapidly after surgery;Patients with diseases abutting critical vasculatures (e.g. carotid artery) where residual disease is anticipated or risk of peri-operative morbidities/mortalities are considered to be high;Patients refuse to undergo potentially mutilating cranio-facial resection due to the consequential functional and cosmetic morbities (e.g. orbital exenteration, total rhinectomy, complete facial nerve sacrifice etc.)

